### Statistical methods

We will use a novel statistical approach [51] implemented by the *NIRStat* R package for analyzing the NIRS data. Specifically, the *NIRStat* method models the observed MES-rSO_2_ time series with a nonparametric smooth function via penalized regression splines [49, 50]. It then provides accurate and robust statistical measures for characterizing the important features in rSO_2_ series. We will use the mean area under the fitted spline curves (MAUC) measure generated from the *NIRStat* package to measure the MES-rSO_2_ levels at baseline and then at post-transfusion. The MAUC changes from baseline to post-transfusion will be used to quantify the changes in MES-rSO_2_ due to transfusion. Two sample t-tests will be used to compare the changes in MAUC between saRBCs +/− pIST. Multivariate linear regression models will also be applied to model the changes in AUC in terms of pIST status (with pIST and without pIST) and other potential confounding factors. The multivariate analysis will allow us to assess whether the changes in MES-rSO_2_ differs significantly between saRBCs with pIST and those without pIST, controlling for other confounding factors.

The incidence of NEC and death will be estimated by the cumulative incidence function appropriate for competing risks. Gray’s method (modified log-rank test) will be used to compare NEC cumulative incidence according to baseline clinical characteristics. Cause-specific hazard ratios will be calculated to measure the degree of association between baseline characteristics and NEC, and between baseline characteristics and death by fitting a stratified Cox proportional-hazards regression model for competing risks. The competing risks model will be implemented using SAS PHREG using robust sandwich covariance matrix estimates to account for within-mother correlation that may occur in outcomes of multiple-birth infants.

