To guard against model overfitting, we will employ both clinical and statistical criteria in making decisions about which independent variables to include; and we will limit the number of candidate variables. In general, the results of models having fewer than 10 outcome events per independent variable are thought to have questionable accuracy and the tests of statistical significance may be invalid. The use of “machine-learning” covariate selection methods, such as bootstrap bagging, will be utilized to improve the reliability of identifying risk factors for NEC and death. The hazard ratio and its 95% confidence interval (CI) will be calculated for each factor in the presence of others in the final model for NEC and mortality.

For metabolomics analysis, we will examine associations between metabolic features of transfused RBC units and pre-transfusion pIST, alterations in MES-rSO_2_, and the development of NEC using an approach previously described [25]. Correlative analyses without pre-selecting specific metabolic pathways will be performed. Methods of analysis will include a number of gene set analysis, such as MSEA and MetaboAnalyst. We can also borrow from the gene expression packages to conduct more complex analysis of metabolite-set differential expression analysis as well as metabolite-set differential coordination analyses. The pathway level analysis will be followed by the detection of metabolites that contribute the most to the changes of metabolic pattern using the built-in scoring system of the packages.

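### Within-mother correlation is allowed for only in the Cox model; the primary MES-rSO2 comparison and Gray's test are specified as if siblings were independent

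*Protocol article*

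**What the plan says.** All of this is in the protocol article.

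- **Cox model.** Statistical methods fits the competing-risks model for NEC and death in SAS PHREG with "robust sandwich covariance matrix estimates to account for within-mother correlation that may occur in outcomes of multiple-birth infants".
- **Primary endpoint.** The same section states "Two sample t-tests will be used to compare the changes in MAUC between saRBCs" with and without pIST, and then "Multivariate linear regression models will also be applied to model the changes in AUC in terms of pIST status" and confounders. Neither sentence mentions clustering.
- **NEC incidence.** Gray's method "will be used to compare NEC cumulative incidence according to baseline clinical characteristics". Again no allowance for clustering is mentioned.
- **Final NEC and mortality model.** "The hazard ratio and its 95% confidence interval (CI) will be calculated for each factor in the presence of others in the final model". This belongs to the regression that carries the sandwich variance.
- **Eligibility.** Study population and eligibility criteria admits every infant at or below 1250 g at the three units, subject to listed exclusions. Being the sibling of an enrolled infant is not one of them.
- **Power.** Sample size estimation takes 110 transfused and monitored infants in two equal pIST groups. Table 1 gives power 0.82 for a 10% difference with SD 18.

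**The concern.** The plan accepts that infants of one mother may not be independent, and then acts on this in one secondary analysis only. A two-sample t-test assumes independent observations, and so do ordinary linear regression and Gray's test in their standard forms. The primary contrast is therefore analysed under an assumption that the same section rejects for NEC and death.

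Two things are at stake. The first is the validity of the primary p-value and interval, in a scenario where the stated power is only just above 80%. The second is the Gray comparison for any characteristic that siblings share by necessity, such as a maternal factor. There, positive correlation makes the ordinary test reject too often, while the Cox result for the same factor is protected.

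**Working it through.** **1. Reproduce the plan's figure.** Inputs from Sample size estimation: 55 infants per group, difference 10, SD 18. The article states no alpha, so two-sided 0.05 is assumed. The noncentral t distribution gives power 0.823 (0.830 by normal approximation), against 0.82 in Table 1. The 72-infant scenario (36 per group, difference 12, SD 18) gives 0.797 against 0.80. The table thus follows from independent infants.

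**2. Margin.** Under the same method, 80% power for 10/18 needs 103.7 independent infants. With 110, power stays at 80% up to a design effect of 110/103.7 = 1.06.

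**3. Effect of siblings on the primary contrast.** Take one record per infant, siblings only as pairs, and equal groups. Let
- m = share of *analysed* infants whose sibling is also analysed,
- ρ = within-pair correlation of the MAUC change,
- c = share of pairs in which both siblings are in the same pIST group.

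The true variance of the difference in means, relative to the variance that the t-test assumes, is

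DE = 1 + mρ(2c − 1).

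The true size of a nominal 5% test is 2[1 − Φ(1.96/√DE)]. The power of a correctly sized analysis follows by replacing SD 18 with 18√DE.

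The article gives none of m, ρ or c. The values below are assumptions.

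| m | ρ | c | DE | true SE / assumed SE | size | power |
|---|---|---|---|---|---|---|
| 0.10 | 0.1 | 1 | 1.01 | 1.005 | 0.051 | 0.82 |
| 0.20 | 0.3 | 1 | 1.06 | 1.03 | 0.057 | 0.80 |
| 0.30 | 0.5 | 1 | 1.15 | 1.07 | 0.068 | 0.77 |
| 0.35 | 0.5 | 1 | 1.175 | 1.08 | 0.071 | 0.76 |
| 0.35 | 0.5 | 0.75 | 1.09 | 1.04 | 0.060 | 0.79 |
| any | any | 0.5 | 1.00 | 1.00 | 0.050 | 0.82 |
| 0.30 | 0.5 | 0 | 0.85 | 0.92 | 0.034 | 0.88 |

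Example, fourth row: DE = 1 + 0.35 × 0.5 × (2 × 1 − 1) = 1.175.

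**4. Check of direction.** The plain t-test was simulated with 110 infants, m = 0.3 and ρ = 0.5 (4,000 runs per case). It rejected a true null in 6.2%, 4.5% and 3.2% of runs for c = 1, 0.5 and 0. This agrees in direction with the formula, and with its values (6.8%, 5.0%, 3.4%) to within 0.6 percentage points.

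**5. Gray's test.** For a characteristic that all siblings share, c = 1 by definition, so positive correlation can only inflate the error rate. For a characteristic on which siblings can differ, the direction depends on concordance, as in step 3. The article does not list the baseline characteristics, so no size is computed for this part.

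**The case against.** **Direction.** The best objection is that pIST belongs to the transfused unit and is recorded for each transfusion (Methods). Nothing in the article says that siblings fall in the same pIST group. If half of the pairs do, the t-test is correct; if most pairs split, it is conservative. This stands. A reader might infer that the planned intervals are too narrow throughout, and the article does not support that. Gray's test yields a p-value, not an interval. The hazard-ratio intervals come from the model with the sandwich variance. Only the MES-rSO2 contrast has an interval that could be wrong, and it could be wrong in either direction.

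**Share of pairs.** A pair counts in the primary contrast only if both siblings are transfused and monitored, and the article assumes that half of the infants are. If 20% to 35% of enrolled infants had an enrolled sibling and transfusion were independent between siblings, m would be 0.10 to 0.175. Even at c = 1 the design effect would then be 1.01 to 1.09 and power 0.79 to 0.82. This also stands, and it is why m is defined on analysed infants and starts at 0.10. Siblings whose need for transfusion is correlated would fall between these values and the enrolled share.

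**Bagging.** The article says that selection methods "such as bootstrap bagging, will be utilized to improve the reliability of identifying risk factors for NEC and death". A reader might infer that infants rather than mothers are resampled. The resampling unit is not stated, and a condensed article may leave it to the full plan, so this is not part of the point.

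**Left to the full plan.** The same defence is weaker for the other analyses. The article does address clustering, confines it to one model, and names for the primary contrast a test that cannot accommodate it.

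**Relevance.** Uncertainty about the SD (9 or 18) and about the number monitored (110 or 72) moves power far more than siblings do. Gray's and Cox p-values also test different quantities, so they need not agree anyway. Both remarks are true and limit the weight of the point, but neither justifies a variance known to rest on a doubtful assumption.

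**Conclusion.** The inconsistency holds. Within-mother correlation is recognised and handled in the Cox model only, while the primary MES-rSO2 t-test and regression and Gray's test are specified as if infants were independent.

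The consequence is modest and has no fixed sign for the primary contrast. With m of 0.10 to 0.35 and ρ of 0.1 to 0.5, all assumed, the design effect is at most about 1.18. That limit requires every pair to share a pIST group; test size is then up to about 7% and power 0.76 to 0.82. The design effect is 1.00 when half of the pairs share a group, and falls to 0.825 (1 − 0.35 × 0.5) when all pairs split.

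The 0.76 is the end of an assumed range. It should not be read as the expected power. The one case with a definite direction is Gray's test by characteristics that siblings necessarily share, where positive correlation inflates the error rate.

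**What to change.** - **Primary endpoint.** Make the linear regression of MAUC change on pIST status the primary comparison in place of the plain t-test, with robust variance clustered by mother. GEE or a mixed model with mother as the cluster would serve equally well.
- **NEC incidence by baseline characteristics.** Replace Gray's p-value, or accompany it, with a mother-clustered test, for example a subdistribution-hazard model with sandwich variance aggregated by mother.

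**Cost.** The mother identifier is already needed for the planned Cox model, so this is a change of analysis options. Intervals will differ slightly and will often be a little wider. There are enough mothers for a robust variance in the primary analysis: with 110 infants and 35% in pairs there are 110 × (1 − 0.35/2) ≈ 91 clusters. The NEC analysis is limited by about 20 expected cases, as the planned Cox model already is.

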##### Study design

We will prospectively investigate, using an established birth cohort design [18, 46], the associations between RBC transfusion (including characteristics of transfused RBCs), anemia, intestinal oxygenation, and NEC. We specifically aim to understand the relationship between pIST, donor RBC metabolomics profiles, and recipient anemia on MES-rSO_2_, as measured by NIRS, and the development of NEC (Fig. 1). Although many studies have characterized the association between NEC and transfusion, none have focused on improving our understanding of the underlying pathophysiology, particularly the intestinal oxygenation changes preceding NEC. Further, the safety and efficacy of various blood banking practices including the preparation of storage-aged RBCs (saRBCs) and repeat donor exposure in recipients remains unclear. The safe threshold of saRBC+/− pIST in infants is not known and longer-stored saRBCs, either before or after irradiation, may potentiate the RBC storage lesion. This study may provide new knowledge regarding the potential benefit or harm of various blood banking practices and may identify new potential mediators of NEC.

The study schema (Fig. 1) illustrates how we aim to characterize the association between metabolic changes in transfused RBCs relative to pIST, and adverse effects in the recipient through two approaches: in vivo NIRS trend monitoring of intestinal oxygenation, and in vitro RBC functional studies. The schema explains how variables will be compared to evaluate primary and secondary endpoints for each specific aim. Our primary endpoint is changes in MES-rSO_2_ trends in response to transfusion of saRBC+/− pIST as measured by NIRS (Aim 1). Secondary endpoints are 1) to determine the hazard ratio of NEC comparing infants transfused with saRBCs with and without pIST; (2) examination of metabolomics fingerprints of transfused RBC (in vitro) among infants with and without NEC (Aim 2); and 3) impact of severity of anemia over time during the NEC window (29–34 weeks postmenstrual age) on MES-rSO_2_ (Aim 3).

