##### Sample size estimation

We aim to enroll a total of 220 infants into the study. We assume 110 of these infants (50%) will receive RBC transfusion and undergo NIRS monitoring. Analysis comparing two groups, divided equally among infants by pIST, would provide more than 80% power to detect a difference of 10% in pre- and post-transfusion mean area under the curve MES-rSO_2_ change (standard deviation = 18) between groups or 90% power to detect a difference as small as 6% in MES-rSO_2_ with a standard deviation of 9 (Fig. 1 and Table 1). However, the number of infants enrolled in the study that receive a transfusion and have NIRS monitoring may be lower than 110. Therefore, we have provided power estimates for analysis of a sample size of 72 infants with RBC transfusion and NIRS monitoring (33% of the enrolled cohort). This will generate 80% power to detect a difference of 12% in pre- and post-transfusion mean area under the curve MES-rSO_2_ change between the two groups if the final sample size is 72 infants (36 per group) and the estimated standard deviation for MES-rSO_2_ change is 18. A secondary analysis evaluating pIST a continuous variable will also be performed, which will likely yield greater power for each of the scenarios presented.

**Table 1 Tab1:** Sample Size and Power Estimates

Groups	*n* = 220 transfused				*n* = 110 transfused				*n* = 72 transfused			
	SD = 9		SD = 18		SD = 9		SD = 18		SD = 9		SD = 18	
Difference in MES-rSO_2_ AUC change (%)	Effect Size	Power	Effect Size	Power	Effect Size	Power	Effect Size	Power	Effect Size	Power	Effect Size	Power
6	0.67	1	0.33	0.69	0.67	0.93	0.33	0.41				
8	0.89	1	0.44	0.91	0.89	1	0.44	0.64				
10	1.11	1	0.56	0.98	1.11	1	0.56	0.82	1.11	1	0.56	0.64
12	1.33	1	0.67	1	1.33	1	0.67	0.93	1.33	1	0.67	0.8

Abbreviations: *MES-rSO*_*2*_ mesenteric regional oxygen saturation, *AUC* area under curve, *SD* standard deviation

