## Methods

All RBC transfusions given to infants during hospitalization will be studied. All RBC transfused units are stored in citrate-phosphate-dextrose-adenine (CPDA-1) preservative solution. pIST and storage days will be recorded for each RBC transfusion. All infants will be monitored with NIRS prior to, during and up to 48 h following each transfusion. Consistent with epidemiologic reports of transfusion-related NEC and prior studies at the 3 centers, we anticipate approximately 20 (10%) infants will develop NEC while on study. For our 2:1 case-controlled metabolomic analysis, we will prospectively analyze 40 infants who do not develop NEC and compare to 20 infants with NEC. Within this sub-cohort, we will compare alterations in metabolic pathways from saRBC unit (in vitro) and infant blood sample (in vivo). We will then examine a third sub-cohort of 120 infants without NEC within the NEC “window” (29–34 postmenstrual weeks’). These infants will also be monitored weekly for 24–48 h with mesenteric NIRS to evaluate the relationship between anemic (hemoglobin < 8 g/dL) and non-anemic infants. Reports suggest that this specific population of infants are more likely to experience paradoxical reductions in MES-rSO_2_ substantially increasing the risk for NEC when transfusions are given [10, 36]. Analysis will also include assessment of hemoglobin as a continuous variable.

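### NEC risk factors are chosen by bagging and then reported with hazard ratios and 95% CIs, although about 20 events support about two variables, and the pIST hazard ratio is not set apart from this selection

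*Protocol article*

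**What the plan says.** - **Events.** Methods: "we anticipate approximately 20 (10%) infants will develop NEC while on study". Sample size estimation: "We aim to enroll a total of 220 infants into the study".
- **Transfused infants.** Sample size estimation: "We assume 110 of these infants (50%) will receive RBC transfusion and undergo NIRS monitoring". As a fallback, "we have provided power estimates for analysis of a sample size of 72 infants with RBC transfusion and NIRS monitoring".
- **Guide on model size.** Statistical methods: "models having fewer than 10 outcome events per independent variable are thought to have questionable accuracy". The section adds that significance tests from such models may not be valid. It also promises clinical as well as statistical criteria and a restricted candidate list, without giving a number.
- **Selection.** Machine-learning methods, "such as bootstrap bagging, will be utilized to improve the reliability of identifying risk factors for NEC and death".
- **Reporting.** "The hazard ratio and its 95% confidence interval (CI) will be calculated for each factor in the presence of others in the final model". This covers both the NEC model and the mortality model.
- **Endpoint.** Study design names as a secondary endpoint to "determine the hazard ratio of NEC comparing infants transfused with saRBCs with and without pIST". The Discussion repeats it.
- **Hazard model.** The only Cox model in Statistical methods relates NEC, and death, to baseline characteristics. Its robust sandwich variance is there for correlation between infants of the same mother.

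**The concern.** Three commitments fit together badly: a small expected event count, a data-driven choice of factors, and final-model estimates with 95% CIs for whatever is chosen. A confidence interval computed as if the final model had been fixed in advance ignores the selection. A factor that survives does so partly because its estimate happened to be large, so its HR is biased away from 1. For a factor with little or no true effect, the interval is also wrong too often.

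The second part is the named secondary endpoint. pIST is recorded for each transfusion during the hospital stay, so it is not a baseline characteristic, and the one hazard model described does not mention it. The text neither exempts pIST from selection nor says that it is a candidate. A reader cannot tell whether the pIST hazard ratio will come from a fixed model or depend on what bagging retains. At stake are the list of NEC risk factors and the interpretation of this endpoint. The primary NIRS comparison is not affected.

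**Working it through.** **1. The plan's own figures.** 10% of 220 is 22, against the stated 20 (20/220 = 9.1%); this agrees within two infants. The alpha level is not stated. Two-sided 0.05 is assumed, because a two-sample t-test at that level reproduces Table 1 (55 per group, difference 10, SD 18: 0.823 against 0.82; 36 per group, difference 12, SD 18: 0.797 against 0.80).

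**2. Variables allowed by the guide (events / 10, rounded down).**
- All infants: 20/10 = 2 (22 events also give 2).
- The pIST contrast exists only in transfused infants. If 110 are transfused and their NEC rate is 10% (assumption): 11 events, 1 variable. With 72: about 7 events, none.
- The Discussion says that 75–90% of low birth weight infants are transfused. If that share applied to the NEC cases (assumption): 0.75 × 20 = 15 to 0.90 × 20 = 18 events, 1 variable.
- If all 20 cases were transfused: 2 variables.

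**3. Precision of a prespecified pIST hazard ratio.** Assume an equal split between pIST groups.
- SE(log HR) = 1/√(events × 0.25).
- Detectable HR at 80% power = exp[(1.960 + 0.842) × SE].
- 20 events: SE = 1/√5 = 0.447; detectable HR = exp(1.253) = 3.5. The 95% CI runs from HR/2.4 to HR × 2.4, since exp(1.96 × 0.447) = 2.4. Power is 34% at HR 2 and 69% at HR 3.
- 11 events: SE = 1/√2.75 = 0.603; detectable HR = exp(1.690) = 5.4; CI factor 3.3.

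**4. What selection does.** An illustrative simulation with assumed settings: 220 infants, 20 events, and 5 or 8 independent candidates, of which one is a binary exposure standing for pIST and the rest are noise. Backward elimination at p < 0.10 was run in 30 bootstrap samples, and factors chosen in at least half of them were kept. The final model was refitted with ordinary 95% CIs. There were 350 replicates with 5 candidates and 150 with 8. Competing deaths and multiple births were not modelled.

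| True HR | Candidates | Exposure kept | Median HR when kept | CI coverage when kept | Selected noise factors with CI excluding 1 |
|---|---|---|---|---|---|
| 1 | 5 | 10% | – | 50% | 34% |
| 1 | 8 | 13% | – | 68% | 39% |
| 2 | 5 | 42% | 3.3 | 95% | 36% |
| 2 | 8 | 45% | 2.8 | 99% | 42% |
| 3 | 8 | 75% | 4.0 | 98% | 36% |

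The coverage figures at HR 1 rest on about 35 and 20 kept replicates (10% of 350, 13% of 150) and are rough. With every candidate null, the final model still held 0.53 (5 candidates) to 0.95 (8 candidates) factors on average. With the exposure alone forced into the model, coverage was 95% to 99%. With 110 infants, 10 events, 5 candidates and a true HR of 2, the exposure was kept in 14% of studies, with a median HR of 4.9.

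So the damage takes two forms. Real effects are omitted or overstated, while null or weak factors get intervals that exclude 1 far more often than the nominal 5%.

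**The case against.** The 10-events guide is cited in the plan as a reason for restraint. It stands beside a promise of clinical criteria and a limited candidate list, and no model size is announced. A reader might infer that the plan breaks its own rule; the text does not show that. What remains is that no limit is fixed, and that a short candidate list does not correct intervals computed after selection.

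A reader might also infer that bagging will remove pIST, or that its interval will be invalid. Neither is supported. Bagging is described for risk factors of NEC and death, the Cox model for baseline characteristics, and nothing makes pIST a candidate. The simulated omission rates apply only if it is one. Where the true HR was 2 or 3, coverage given selection was 95% to 99%, so the interval failure belongs to null or weak factors.

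Three further limits stand. The number of candidates and the selection threshold are assumptions. The document does not show that anemia determines which pIST an infant receives; it presents anemia as acting together with stored or irradiated cells, so anemia cannot be called the main confounder. The plan makes no power claim for NEC, so low power contradicts nothing stated.

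Model terms and retention rules are often left to a full analysis plan, and their absence alone would be no finding. Here the article does choose a selection method and a way of reporting its result, and that choice can be judged against the article's own event count.

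**Conclusion.** The concern holds in limited form and should be acted on. The stated method selects NEC factors from data with about 20 events and reports an HR and 95% CI for each survivor. The only variance correction described is for multiple births. Under the assumed simulation settings with 20 events, a true HR of 2 is reported with a median of 2.8 to 3.3 when the factor is selected, and 34% to 42% of selected noise factors have a CI excluding 1. These sizes depend on the assumed candidates and thresholds; the direction does not.

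The event budget is about two variables overall and nearer one for the pIST contrast, depending on how many NEC cases are transfused. The pIST hazard ratio is left unprotected rather than planned to be dropped. Even in a fixed model it can only be an estimate with a wide interval.

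**What to change.** - Estimate the pIST hazard ratio in transfused infants from a small prespecified cause-specific Cox model. Always keep pIST and treat it as time-varying, since it is recorded for each transfusion. Use no data-driven selection.
- Add at most one prespecified adjustment term, such as pre-transfusion hemoglobin, and only if the number of events in transfused infants allows it under the plan's guide.
- Keep the within-mother robust variance. If events are sparse, add a penalized fit as a sensitivity analysis rather than as a replacement.
- Report the bagging results as exploratory, either as inclusion frequencies or with bootstrap intervals that repeat the whole selection in each resample.
- State that the pIST hazard ratio is for estimation, with the detectable HR of about 3.5 at 20 events and about 5.4 at 11 under an equal split.

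The cost is a change of wording in the Statistical methods section, with no new data or patients. The downside is that fewer adjusted factors are reported as confirmatory, which the plan's own guide already implies.
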